## Methods

### Scale Development and Measures

The PRIDE Scale included 39 new test items examining LGBTQI+ health care knowledge, awareness, attitudes, skills, and the work environment,. Development of these items was iterative and generated through literature reviews, expert consultation, and adaptation from existing scales. The Delphi method was used to select the most relevant items via iterative rounds of feedback from an expert panel. The first step was to identify and recruit a diverse group of international experts with relevant experience in LGBTQI+ health care, psychometric scale development, and clinical competence. These experts included health professionals (mostly physicians and psychologists), LGBTQI+ health advocates, clinicians, researchers, public health professionals with expertise in biostatistics and epidemiology, and educators. In total, the panel was comprised of 12 members. There were 3 Delphi rounds. In the first round of item generation, experts on the study team developed a broad number of items (100) both from the existing literature and newly formed items, which were then randomly listed and presented to the expert panel. Experts were asked to evaluate each item based on its relevance, clarity, and its potential importance for measuring LGBTQI+ related competencies among health care professionals. Experts could also comment on each item and suggest new or adapted items. After the first round, responses were scored for relevance and ordered accordingly. Quantitative consensus was defined a priori as a threshold of ≥75% and a median rating of ≥4 on a 5-point scale indicating an item as important or very important. These thresholds align with accepted Delphi standards and ensure that retained items reflect high agreement and rating stability. Based on the scoring (1-100), 39 items that showed strong consensus for inclusion were retained. These items are measured on a 5-point Likert-style scale that ranges from 1 (strongly disagree) to 5 (strongly agree).

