### Statistical Analysis

#### Analytical Methods

All analyses will be performed using Stata (v.17) and R (v.4.5.1; R Foundation for Statistical Computing); Figure 2 shows the planned statistical analysis flowchart. We begin by analyzing the distributions of scale items. Continuous variables will be analyzed using descriptive statistics such as mean, median, standard deviation, quartiles, and IQRs, while for categorical variables, frequencies, proportions, or percentages will be used. Given the probable nonnormal distribution of items and scale scores, numerical comparisons will be performed using Dunn [40] test for stochastic dominance among multiple pairwise comparisons, following a Kruskal-Wallis test of stochastic dominance among k groups [41]. We will use EFA and CFA to identify dependence structures among measures, and item response theory (IRT) to explore factor diagnostics and retain items that carry the greatest exploratory power. Validation analyses will be conducted using the Kruskal-Wallis test with Bonferroni correction for multiple comparisons.

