**Figure 2. F2:**
[figure not shown]
Professional Readiness in Diversity and Equity (PRIDE) scale statistical analysis plan for scale evaluation. CFI: comparative fit index; GRM: graded response model; ML: maximum likelihood; RMSEA: root mean square error of approximation; SRMR: standardized root mean square residual; TIFs: test information functions; TLI: Tucker-Lewis index.

Missing data will be assessed prior to all analyses. For the United States sample, participants were required to fill all survey items, with branching (skip) logic implemented for respondents who did not currently engage in clinical practice. For the European sample, participants were permitted to skip responses for demographics only. We concatenated all complete and partial responses and participants with more than 10% of items missing will be excluded. For the remaining participants, missing values in the CFA framework will be handled using full information maximum likelihood estimation [42,43]. Descriptive and known-groups validity analyses will use pairwise deletion. The proportion and pattern of missing data will be reported, and missing completely at random test by Little will be used to evaluate the missing data mechanism.

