#### EFA and CFA

EFA will be conducted to examine the underlying dimensional structure of the PRIDE scale and to inform item retention. As an initial parametric approach, EFA will be performed using principal component analysis (PCA) with varimax (orthogonal) rotation to obtain a simple and interpretable factor solution. Prior to extraction, the suitability of the data for factor analysis will be assessed (eg, inspection of the correlation matrix and standard measures of sampling adequacy). The number of factors to retain will be determined using the Kaiser criterion (eigenvalues ≥1) in conjunction with visual inspection of the scree plot to identify the point of inflection. Items will be evaluated based on their pattern of loadings, and only items with primary factor loadings ≥0.40 will be considered for inclusion. Items showing substantial cross-loadings (eg, ≥0.30 on more than 1 factor) or weak or unstable loadings will be reviewed for removal or revision, with decisions guided by both statistical evidence and conceptual coherence with the intended constructs. Given the ordinal nature of Likert-type responses, a complementary nonparametric ordinal approach will also be implemented. Specifically, a polychoric correlation matrix will be estimated and subjected to factor analysis with varimax rotation, applying the same factor-retention rules (eigenvalues ≥1 and scree plot) and item-selection criteria (primary loading ≥0.40, limited cross-loading). Consistency of the factor structure across the PCA-based and polychoric-based solutions will be examined to strengthen inferences regarding dimensionality and to ensure that the final factor model is robust to distributional assumptions. We acknowledge that PCA is technically a data-reduction technique that accounts for total item variance rather than modeling shared latent variance exclusively, and therefore does not constitute a latent variable model in the strict sense [30,44]. Its use here is pragmatic, consistent with its established role as an initial item-selection tool at the exploratory stage. The robustness of the dimensional solution will be evaluated formally through the planned cross-validation against the polychoric-based factor solution and, most importantly, through the subsequent CFA with maximum likelihood estimation, which will constitute the primary evidence for the latent structure of the PRIDE Scale.

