CFA will be used to confirm the factor structure identified in the EFA. Model fit will be evaluated using the following indices: chi-square statistic, comparative fit index (CFI), root mean square error of approximation (RMSEA), standardized root mean square residual (SRMR), Tucker-Lewis index, Akaike information criterion, and Bayesian information criterion will be used following cutoff recommendations by Hu and Bentler [45,46].

To establish the cross-cultural and cross-demographic equivalence of the PRIDE Scale, formal measurement invariance testing will be conducted using multigroup confirmatory factor analysis. Following the sequential approach recommended by Vandenberg and Lance [47] and Putnick and Bornstein [48], configural invariance (same factor structure across groups), metric invariance (equal factor loadings), and scalar invariance (equal item intercepts) will be tested sequentially across two sets of planned comparisons: (1) Italian-speaking and English-speaking (United Kingdom and United States combined) subsamples, to establish cross-linguistic and cross-national measurement equivalence; and (2) LGBTQI+ and cisgender heterosexual participants, to evaluate whether the scale functions equivalently across groups that differ in sexual orientation and gender identity; a particularly important consideration given the nature of the construct being measured. Model comparisons will be evaluated using the chi-square difference test and changes in CFI (ΔCFI ≤−0.010) and RMSEA (ΔRMSEA ≤0.015) as criteria for invariance [49]. Additional subgroup analyses will be conducted to assess the potential influence of professional background (student vs trained practitioner) and gender on the validity of the CFA solution [50]. Where measurement invariance testing reveals a failure of scalar invariance for specific items, differential item functioning (DIF) analyses will be conducted as a planned follow-up to identify items performing differently across subgroups. DIF will be evaluated using ordinal logistic regression, which enables the detection of both uniform and nonuniform DIF for polytomous Likert-type items. Items exhibiting significant and practically meaningful DIF will be flagged for review during subsequent scale refinement.

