### Limitations

Several limitations should be acknowledged. First, the convenience sampling approach, supplemented by snowball recruitment through professional mailing lists, LGBTQI+ associations, conferences, and institutional teaching sessions, limits the generalizability of the findings to the broader health care workforce in Italy, the United Kingdom, and the United States. To partially mitigate this, the sample demographics will be benchmarked against national statistics. Relatedly, the recruitment strategy is susceptible to network bias: health care professionals with preexisting interest in LGBTQI+ health may be overrepresented, while less engaged or less supportive professionals may be underrepresented, potentially attenuating variability in key constructs and inflating estimates of health care professional readiness and of an inclusive climate. The reliance on self-report measures further introduces social desirability bias, as participants may respond in ways that align with professional norms rather than their actual beliefs, knowledge, or behaviors; anonymous administration reduces but does not eliminate this concern.

Second, although the instrument was developed and administered in multiple languages across 3 national contexts, translation and cross-cultural adaptation processes inevitably introduce subtle semantic and conceptual differences across versions. While measurement invariance testing and Differential Item Functioning analyses will identify items that function differently across linguistic, cultural, or demographic groups, some degree of construct nonequivalence may persist, particularly given the heterogeneous legal, cultural, and clinical frameworks governing LGBTQI+ health across the participating countries.

Third, the Delphi expert panel, while interdisciplinary and international, comprised 12 members, and consensus-based item generation is inherently shaped by the perspectives, disciplinary backgrounds, and sociocultural positioning of the panelists. Although the 75 percent consensus threshold and 3-round structure were designed to enhance rigor, alternative panel compositions might have yielded different item pools, particularly regarding emerging or contested constructs within LGBTQI+ health.

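### The primary CFA uses maximum likelihood, with no robust or categorical variant named, on items the plan calls ordinal and probably nonnormal; under clear skew its chi-square and metric-invariance tests over-reject

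*Protocol article*

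**What the plan says.** The section EFA and CFA concedes that the initial principal component step is not a latent variable model. It places the weight on what follows: "through the subsequent CFA with maximum likelihood estimation, which will constitute the primary evidence for the latent structure of the PRIDE Scale". The missing-data paragraph after Figure 2 is consistent with this: "missing values in the CFA framework will be handled using full information maximum likelihood estimation". Invariance is then tested in sequence, the third step being "scalar invariance (equal item intercepts". That is the parameterisation of a linear model for continuous items; an ordinal model would have thresholds. Fit is judged by several indices, among them "chi-square statistic, comparative fit index (CFI), root mean square error of approximation (RMSEA". Invariance is judged by the chi-square difference test and by changes in CFI (0.010) and RMSEA (0.015), with no rule for combining the three.

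On the data, Scale Development and Measures says "These items are measured on a 5-point Likert-style scale that ranges from 1 (strongly disagree) to 5 (strongly agree". Analytical Methods opens its choice of group comparisons with "Given the probable nonnormal distribution of items and scale scores". EFA and CFA justifies a second, polychoric exploratory analysis with "Given the ordinal nature of Likert-type responses, a complementary nonparametric ordinal approach will also be implemented". Limitations warns that engaged professionals may be overrepresented, "potentially attenuating variability in key constructs and inflating estimates of health care professional readiness".

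**The concern.** Ordinal methods are planned for the complementary exploratory analysis, the graded response models, ordinal alpha and the differential item functioning (DIF) analysis. The step called primary is the one without such a method.

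Two separate faults can follow.

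- **Nonnormality.** The reference distribution of the maximum likelihood chi-square assumes normal data. Skewed, heavy-tailed items inflate it.
- **Linearity.** A linear model cannot reproduce items that flatten at the top category. Two groups with identical loadings and thresholds but different latent means can then show different linear loadings. They appear non-invariant because of the response format.

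At stake is the comparability claim across languages and across LGBTQI+ and cisgender heterosexual respondents. The article calls the second comparison particularly important. It is also the one where latent means may well differ.

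The plan's ordinal check would not reliably catch the error, because DIF analysis is triggered only by a scalar failure, while the false alarms arise mainly one step earlier.

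**Working it through.** **Inputs from the article.** There are 39 items with 5 categories. The sample-size rule reproduces exactly: 39 × 5 = 195 and 39 × 10 = 390. No error rate or power is stated for the CFA, so there is no further figure to reproduce. The survey had 1339 completers, split 50/50, so Split B has 1339 / 2 = 669.5, about 670, before the exclusion for more than 10% missing.

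**Assumptions, not in the article.**
- A 5% level for these tests (0.05 is stated only for test-retest).
- Cutoffs of CFI 0.95 and RMSEA 0.06 (the cited ones are not printed).
- Four factors, loadings 0.55 to 0.80, factor correlation 0.4, and 20 or 36 retained items.
- Multigroup analysis in Split B, with two groups of 335 and 20 items.
- Latent normal responses cut into five categories with these shares (categories 1 to 5):
  - A, symmetric: .07, .24, .38, .24, .07
  - B, moderate skew (skewness about −1.0): .03, .07, .15, .35, .40
  - C, ceiling (skewness about −2.2): .02, .03, .05, .20, .70
  - D: A, B and C mixed across items
  - N: uncut normal control

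**Degrees of freedom.** df = p(p+1)/2 − (p loadings + p residual variances + 6 correlations). With 20 items this is 210 − 46 = 164; with 36 items it is 666 − 78 = 588. The metric step adds 20 − 4 = 16.

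**True single-group model, N = 670, rejected at 5% (%).** 400 runs for 20 items, 150 for 36.

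| Items | ML, 20 items | ML, 36 items | Scaled (Satorra-Bentler), 20 items |
|---|---|---|---|
| N | 7.0 | 8.0 | 7.7 |
| A | 5.8 | 7.3 | 5.8 |
| B | 27.0 | 72.7 | 6.2 |
| C | 91.5 | 100 | 7.0 |
| D | 44.8 | 93.3 | 15.0 |

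Why the chi-square fails while RMSEA does not: with 588 df the 5% critical value is 645.5, a chi-square/df ratio of 645.5 / 588 = 1.10. The mean ratios with 36 items were 1.14 (B), 1.20 (D) and 1.45 (C), all beyond it. But RMSEA = √[(ratio − 1)/(N − 1)], so even 1.45 gives √(0.45/669) = 0.026. Reaching 0.06 would need a ratio of 1 + 669 × 0.0036 = 3.41. RMSEA exceeded 0.06 in 0% of runs everywhere. CFI fell below 0.95 only in C (1.5% with 20 items, 18.7% with 36).

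**Two truly equal groups, false failure (%) at latent mean differences 0 / 0.5 / 0.8 SD.** 150 runs each.

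| Items | Metric, ML difference | Metric, CFI drop > 0.010 | Metric, scaled difference | Scalar, ML difference |
|---|---|---|---|---|
| A | 2.0 / 2.7 / 2.0 | 0 / 0 / 0 | 5.3 / 4.7 / 4.7 | 4.7 / 4.7 / 2.7 |
| B | 11.3 / 24.0 / 38.7 | 0 / 0.7 / 2.0 | 4.7 / 5.3 / 6.7 | 4.0 / 7.3 / 8.0 |
| C | 68.0 / 88.0 / 96.0 | 15.3 / 54.7 / 78.7 | 2.0 / 2.7 / 6.0 | 6.0 / 7.3 / 15.3 |
| D | 18.7 / 90.0 / 100 | 0.7 / 50.7 / 95.3 | 4.7 / 66.0 / 98.0 | 6.0 / 10.7 / 24.0 |

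The change in RMSEA exceeded 0.015 in at most 2.7% of runs. The configural chi-square rejected in 11% to 15% (A), 50% to 73% (B), 100% (C) and 65% to 92% (D), against 8.7% for the normal control.

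Monte Carlo standard error is √(0.05 × 0.95/150) = 1.8 points near 5% and √(0.25/150) = 4.1 points near 50%, smaller with 400 runs.

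Scaling removes the nonnormality fault (B, C). It does not remove the linearity fault, which appears in D once group means differ. A categorical estimator addresses that fault directly but was not simulated.

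**The case against.** The case against has several parts.

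- **Certainty.** A reader might infer that correct models and equal groups will be rejected whatever the data look like. The documents do not support that. The article says only that nonnormality is probable, and its remarks on overrepresentation are hedged. With symmetric items the single-group rate is 5.8% to 7.3% and the metric rate 2% to 3%. This stands, and the point is conditional on skew. The 0.5 and 0.8 SD group differences are also assumed.
- **Several indices.** A reader might infer that the primary CFA would be declared a failure. The article does not judge on chi-square alone, and RMSEA, and CFI except under heavy ceiling, would pass the correct model. This stands for the single-group CFA. It helps less for invariance: under C and D with unequal means, two of the three named criteria fail together and no rule says which prevails.
- **Scalar step.** The equal-intercepts wording tempts one to place the damage there. The rates do not show it: 4% to 6% with equal means and at most 24% otherwise.
- **Item loss.** A reader might infer that sound items would be dropped automatically. Removal needs combined evidence from Mokken, CFA and graded response results, and items with DIF are only flagged for review. The realistic harm is equivalence wrongly denied.
- **Condensed article.** Maximum likelihood does not exclude a robust test statistic, and no multigroup estimator is named; that part is inferred from the intercept wording and the full-information method. A robust correction could sit in a fuller plan. A categorical estimator would hardly be described in these terms.

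**Conclusion.** The concern holds in conditional form. Maximum likelihood with a linear-intercept invariance model is a stated choice, and it sits badly with the article's own description of its items as ordinal and probably nonnormal.

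Under moderate to heavy skew, the unadjusted chi-square rejects a correct 20-item model in 27% to 92% of runs. The metric-step difference test rejects truly equal groups in 11% to 100%. The CFI change is a false alarm in 51% to 95% under heavy ceiling or mixed skew with means 0.5 to 0.8 SD apart, but in no more than 2% under moderate skew. RMSEA is barely affected and the scalar step only modestly; with roughly symmetric items there is little problem.

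These sizes rest on the assumed category shares, loadings, item counts, equal group sizes, 5% level and fit cutoffs. The direction rests on the article's own expectations. The change should be made before the analysis scheduled for Summer 2026, but it does not undermine the study.

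**What to change.** 1. For the Split B CFA and the multigroup CFA, name a categorical estimator: WLSMV on polychoric correlations, testing loadings and thresholds in place of intercepts, with scaled difference tests.
2. Report robust maximum likelihood (MLR, scaled tests) with full-information handling of missing values beside it. At minimum, replace the unadjusted tests by robust scaled ones.
3. Run the ordinal DIF analysis after a metric failure as well as after a scalar failure.

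The cost is wording and code in R, which is already planned; no new data are needed. The downsides should be stated:
- Sparse low categories may need collapsing, identically across groups.
- The CFI and RMSEA change cutoffs are less well calibrated under WLSMV, which is a reason to show both estimators.
- Robust maximum likelihood alone does not cure false metric failure when thresholds differ between items and means differ between groups (66% and 98% in D).
- Giving up full-information estimation in the primary model is not free. The 39 items were required fields, but partial responses with up to 10% of items missing are kept and US respondents outside clinical practice followed skip logic. The handling of both in the WLSMV model must be specified.

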### Study Population and Sample

The study population consisted of health professionals, including students or health professionals-in-training, such as physicians, nurses, and other allied health professionals (eg, podiatrists, occupational therapists, physiotherapists, and mental health professionals) working in Italy, the United Kingdom, and the United States, with respondents able to complete the survey in English or Italian, depending on the country. The goal was to have a norming sample of international health care professionals including those in-training.

Sample size was calculated considering the 2 main statistical techniques to be used in the analysis: exploratory factor analysis (EFA) and confirmatory factor analysis (CFA). Based on the literature, as a rule of thumb (item-to-participant ratio), 5 to 10 participants per item are required [29-32]. For the 39-item PRIDE scale, this would translate to a minimum of 195 participants (5 participants per item) and a preferred sample size of 390 participants (10 participants per item). However, as we are planning an EFA and CFA, a total of approximately 700 participants is planned. For test-retest reliability, based on Walter et al [33], and assuming a null intraclass correlation coefficient of 0.40, an expected intraclass correlation coefficient of 0.70, 2 administrations of the scale, a significance level (α) of 0.05, and a power (1–β) of 0.80, a sample size of 62 is required.

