#### Reliability Estimates and Test-Retest Reliability

Internal consistency reliability for the PRIDE scale will be evaluated within each sample (United States and Europe) and reported for each subscale, and for the total scale only if a defensible higher order or general-factor model supports total scoring. Reliability will be quantified using Cronbach α and, for ordinal Likert-type items, ordinal alpha (α_ord) computed from a polychoric correlation matrix. In addition, McDonald omega (ω) will be estimated for each monotone or unidimensional subscale using a congeneric factor model (allowing heterogeneous item loadings) and will be treated as the primary model-based estimate; where relevant, omega estimates derived under an ordinal framework (polychoric correlations or appropriate ordinal estimators) will be reported. Item-total correlations will be examined to assess the contribution of individual items to subscale reliability, and items with low item-total correlation (eg, <0.30) will be flagged for potential removal in conjunction with evidence from MSA, CFA (factor loadings or model fit), and IRT GRM outputs (discrimination, thresholds, and information), in accordance with the prespecified item selection rules. Test-retest reliability correlations will establish temporary (2-wk) stability of the PRIDE Scale using the blinded combined United States and European samples pooled. The test-retest sample size power calculation suggested an ideal sample size of 62 for this reliability test.

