## Discussion

### Principal Findings

The development and validation of the new PRIDE scale will represent a significant advancement toward improved cultural competence among health care professionals in Europe and the United States. Validating the scale in English- and Italian-speaking populations will support the development of international interventions and, ultimately, treatment outcomes for LGBTQI+ people globally.

The PRIDE Scale is anticipated to make several distinct contributions to the field of LGBTQI+ health and to the broader science of clinical competency assessment. First, it will provide a contemporary, psychometrically robust instrument that reflects current language, conceptual nuance, and lived realities of LGBTQI+ communities, addressing well-documented limitations of existing tools. Currently, the most frequently used measure of health care professionals’ knowledge and attitudes toward LGBTQI+ individuals is the LGBT-DOCSS, developed nearly a decade ago [21,22], which no longer fully reflects contemporary language, concepts, or understandings of LGBTQI+ identities. Due to evolving cultural norms, some of the LGBT-DOCSS terminology is now perceived as outdated and, in some cases, offensive by survey-takers. The PRIDE Scale will enable researchers to build on the contributions of the LGBT-DOCSS while modernizing the language and explicitly incorporating perceptions of workplace climate, which has been shown to shape patient outcomes [55]. Second, by being developed and validated simultaneously across 3 countries and 2 languages, the PRIDE Scale is positioned as one of the few internationally validated LGBTQI+ competency measures, with formal measurement invariance testing supporting cross-cultural comparability. Third, by integrating individual-level competence (knowledge, attitudes, awareness, and skills) with organizational climate, the scale operationalizes a more ecological understanding of clinical care, consistent with growing evidence that workplace context shapes health care professional behavior and patient experience [25-27]. Fourth, the instrument is expected to function both as a research outcome measure (eg, for educational and organizational interventions) and as a practical self-assessment and quality-improvement tool in clinical and training settings.

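### UK–US equivalence is never tested and the Italian form gets no reliability coefficient of its own, although the article claims validation across three countries and two languages

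*Protocol article*

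**What the plan says.** Four parts of the Protocol article bear on this.

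- **EFA and CFA, invariance.** Configural, metric and scalar invariance "will be tested sequentially across two sets of planned comparisons". The first comparison is "Italian-speaking and English-speaking (United Kingdom and United States combined) subsamples, to establish cross-linguistic and cross-national measurement equivalence". The second is "LGBTQI+ and cisgender heterosexual participants, to evaluate whether the scale functions equivalently across groups that differ in sexual orientation and gender identity".
- **EFA and CFA, other subgroup work.** Additional analyses address the "potential influence of professional background (student vs trained practitioner) and gender on the validity of the CFA solution". Differential item functioning (DIF) analysis is conditional: "Where measurement invariance testing reveals a failure of scalar invariance for specific items".
- **Reliability Estimates and Test-Retest Reliability.** Internal consistency "will be evaluated within each sample (United States and Europe", the bracket naming the two strata. Test-retest reliability is estimated on both samples pooled.
- **Principal Findings.** The scale is presented as distinctive "by being developed and validated simultaneously across 3 countries and 2 languages", with invariance testing cited in support of comparability across cultures.

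Study Population and Sample describes recruitment in Italy, the UK and the US, "with respondents able to complete the survey in English or Italian, depending on the country". The PRIDE Survey section says that the Italian version was translated and back-translated.

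**The concern.** The UK changes partner between analyses. It is grouped with the US for invariance and with Italy for internal consistency. Two consequences follow.

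First, UK versus US is the one contrast in these data that varies country while holding language fixed, and pooling removes it. The first comparison is nevertheless said to establish equivalence across nations as well as languages. The instrument includes workplace climate items, and the Limitations section itself notes that legal, cultural and clinical frameworks differ among the participating countries. A UK–US difference on some items is therefore plausible.

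Second, the Italian form is the only translated form, and the plan yields no internal-consistency coefficient specific to it. A user of the Italian version would have only a European figure that also contains UK respondents answering in English.

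At stake is whether UK and US scores may be compared, and whether the Italian form's precision is known.

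**Working it through.** **1. Which listed analysis isolates which group?**

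| Analysis | Grouping stated | Isolates UK vs US? | Isolates Italian form? |
|---|---|---|---|
| Invariance comparison 1 | Italian vs (UK + US) | No | Yes (structure, loadings, intercepts) |
| Invariance comparison 2 | LGBTQI+ vs cisgender heterosexual | No | No |
| Extra CFA subgroups | Student/practitioner; gender | No | No |
| DIF | Only after scalar failure in a tested comparison | No | Only if comparison 1 fails |
| Alpha, ordinal alpha, omega | US; Europe (UK + Italy) | Separate estimates, but UK mixed with Italy | No |
| Test-retest | All pooled | No | No |

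Three countries give 3 pairwise contrasts. The plan runs one contrast, and it pools two of the three countries. Country is otherwise used for the random split, the balance checks and benchmarking against workforce statistics (Statistical Analysis), so it is recorded.

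**2. Do equal loadings give equal reliability?** For a one-factor subscale with loadings λ, factor variance ψ and residual variances θ,

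omega = (Σλ)²ψ / [(Σλ)²ψ + Σθ].

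Metric and scalar steps constrain loadings and intercepts. The sequence stops there, leaving ψ and θ free. Passing comparison 1 therefore does not fix the Italian omega.

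**3. Can masking happen?** The values here are assumed and show possibility only.

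*Intercepts.* Let a UK item intercept lie 0.5 above Italy and the US one 0.5 below, a UK–US gap of 1.0. With UK share p of the English group, pooled English minus Italy = 0.5p − 0.5(1 − p):

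- p = 0.3: −0.2
- p = 0.5: 0.0
- p = 0.7: +0.2

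*Reliability.* Take 8 items with equal standardised loadings, so inter-item correlation r = loading² and alpha = 8r/(1 + 7r).

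- Italy, loading 0.40: r = 0.16, alpha = 1.28/2.12 = 0.60
- UK, loading 0.75: r = 0.5625, alpha = 4.5/4.9375 = 0.91

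With equal means, the European r is the share-weighted average of the two:

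| Italy's share of Europe | r | Pooled alpha |
|---|---|---|
| 25% | 0.462 | 0.87 |
| 50% | 0.361 | 0.82 |
| 75% | 0.261 | 0.74 |

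A mean difference of 0.5 SD raises these to 0.88, 0.84 and 0.77.

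**4. Are the groups large enough to separate?** The article gives 1339 completers with no country split, and a minimum of 5 participants per item, which is 5 × 39 = 195. Assume that invariance is run in Split B (1339/2 = 669.5) and that the rule applies to each group. A country then needs 195/669.5 = 29% of all respondents to reach 195. Over an assumed range of shares:

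| Country share | Full sample | Split B | Items allowed in Split B at 5 per item |
|---|---|---|---|
| 10% | 134 | 67 | 13 |
| 20% | 268 | 134 | 26 |
| 33% | 442 | 221 | 39 (all) |

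**The case against.** The best defence has four parts.

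- **The Italian form is tested.** Comparison 1 requires the factor model to hold in the Italian group and compares its loadings and intercepts with the English ones. A reader might infer that the plan cannot support validation in Italian at all. The document does not bear that out; what is missing is a separate reliability coefficient.
- **Language and country cannot be disentangled for Italy by any analysis.** The article names both aims for one contrast and never says that it separates them. This stands. The criticism is that the national half of the aim is only partly served, because UK versus US is left out.
- **Pooling may be prudent.** A separate UK group could fall below 195 in Split B, with a risk of non-convergence. This also stands, so a three-group model must depend on the numbers. It does not justify stating the unrestricted claim.
- **The US/Europe strata have a rationale.** The survey was run in US and European versions, with differences in demographic items, consent presentation and skip rules. That explains the strata but gives no figure for the translated form. The wording changes described concern screening and demographics, so they are not evidence that PRIDE items differ.

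The Limitations section also concedes that some non-equivalence may persist. That softens the claim, but it relies on invariance and DIF analyses to identify differing items, and these do not reach UK versus US.

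**Conclusion.** The point holds as a mismatch between stated groupings and stated claim. UK–US equivalence is untested, DIF cannot reach it, and the Italian form receives no alpha or omega of its own. This follows from the text and needs no assumption.

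The size of any masked difference cannot be given, because counts by country are absent. A reader might infer that a UK-specific difference would go undetected, or might attach a diluted loading shift to it. The documents support neither, since that would need country shares and a detection calculation. The figures above show only that a sizeable gap can cancel and that a weak Italian coefficient can sit inside an acceptable European one. They depend on assumed loadings, intercepts and shares; with Italy at 75% of Europe the pooled alpha already falls visibly, to 0.74.

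This should be corrected, but it does not undermine the factor-analytic plan as a whole.

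**What to change.** - Report alpha, ordinal alpha and omega by language, and by country where numbers allow.
- Add a UK versus US invariance contrast, or replace comparison 1 with a three-group Italy/UK/US model. If the UK group is small, run it on the retained items or subscale by subscale. Let a scalar failure there trigger the DIF analysis already planned.
- Describe Italian versus English as language and country combined.
- State the counts by country. If the UK group is too small to test, limit the cross-national claim and say that UK–US equivalence was not examined.

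The cost is a few more model runs on data already collected. The drawbacks are less precise estimates and possible non-convergence in the smallest country group. Because recruitment has closed, the additions should be recorded as made after data collection.
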